## Methods

### Overall design and timeline

The current study will employ a multi-site, longitudinal, blinded randomized controlled trial (RCT) design with a target sample of 120 older adults without dementia or MCI (see inclusion criteria below). Sixty older adults completing TAPAT will be compared to sixty older adults completing the active control condition (computer-based games; see Fig. 1). Total participation time is approximately 6 months and includes 5 in-person assessment sessions. Assessments will be performed at University of Iowa (Iowa City, IA) and VA Boston Healthcare System (Boston, MA). The first assessment session (V0) involves screening for eligibility (see inclusion/exclusion below). If the participant is eligible, baseline assessments are administered in a second visit (V1) to characterize their cognitive and functional abilities before training. After the baseline assessment, older adults are randomized to either the TAPAT or control training program and complete approximately 12–16 weeks of in-home training, while monitored and coached by a research assistant (*cognitive remediation coach*). Participants assigned to the experimental software treatment program will be randomly assigned to receive performance feedback (version A.1 vs. A.2) in the first or the second half of training. Participants will then be asked to complete a mid-training assessment (V1.5) and will be administered a subset of assessments comprised of the secondary outcome: mindfulness. At the mid-training assessment, participants who were randomized to the experimental program will switch program versions (i.e., participants that trained on version A.1 will begin version A.2, and vice versa), such that participants train on both versions. To measure potential training-related improvements, participants will be assessed immediately after the completion of the total training (V2) by an assessor that is blind to group affiliation. To measure the persistence of potential training-related improvements, participants are also assessed after a three-month no-contact period (V3), again by an assessor blind to group affiliation. After this visit, participant activities are completed and trial participation ends.

**Fig. 1 Fig1:**
[figure not shown]
Study Outline

### Study population

The study population is comprised of healthy older adults with axiomatic age-related cognitive decline. Due to the average age of individuals with age-related cognitive decline (i.e., 60–90 years old), we expect this population to have additional challenges, including but not limited to vision and/or hearing difficulties, motor difficulties, and other unrelated, pre-morbid medical complications. We will only enroll individuals for whom these complications will not interfere with assessment procedures or completion of the training programs.

The following inclusion/exclusion criteria will be determined through our screening procedures during V0, which includes structured interviews, as well as computerized and standardized neuropsychological assessments of attention, cognition and functional abilities.

#### Inclusion criteria

65 years of age or older at the time of consentFluent spoken English by the age of 12 in the judgment of the consenting clinician or as verified via participant interview.Participants must have adequate sensorimotor capacity to participate in the trial, including visual capacity, auditory capacity, and motor capacity adequate to control a computer mouse.Age-related cognitive status will be confirmed through performance on the Montreal Cognitive Assessment (MoCA). Participants must score a 26 or above on the MoCA.

#### Exclusion criteria

Diagnosis of PTSD, depression or other psychologically diagnosable emotional disorder as verified via participant self-report, and performance on the Geriatric Depression Scale (GDS ≥ 20). If the participant has previously had a psychologically diagnosable Axis I emotional disorder and they have not experienced an episode for more than 2 years, they may be included.Diagnosis of an illness or condition with known cognitive consequences (e.g., schizophrenia, bipolar disorder, cancer, multiple sclerosis) will be excluded due to the confound with cognitive impairment from those conditions. If the participant has received 5 or less doses of chemotherapy in the two years preceding potential enrollment, they may be included. These exceptions are up to the discretion of the Study Principal Investigator and Site Principal Investigators.Participants who have answered ‘yes’ to:
Question 5 (Active Suicidal Ideation with Specific Plan and Intent) on the Columbia-Suicide Severity Rating Scale (C-SSRS) or,‘Yes’ to any of the suicide-related behaviors (actual attempt, interrupted attempt, aborted attempt, preparatory act or behavior) on the “Suicidal Behavior” portion will be excluded from the study *if the ideation or behavior occurred within two months from Participant’s date of consent* (as recommended by the FDA for treatment trials.) Participants excluded for this reason will be referred for appropriate treatment. Further, participants meeting this criteria at any time throughout the study will be asked to complete a final assessment, if appropriate, then withdrawn from the study and referred for appropriate treatment.
4)Current or significant past history of substance abuse in the judgment of the Site PI.5)Difficulty completing assessments and/or comprehending requirements of the trial (e.g., following verbal instructions).6)Enrollment in a concurrent clinical trial involving an investigational pharmaceutical, nutraceutical, medical device or behavioral treatment that could affect the outcome of this study will be excluded. Participants will not be excluded for participation in conventional treatments (e.g., physical or occupational therapy) or use of prescribed medications.

#### Recruitment

Each study site has pre-existing recruitment methods specific to the normally aging population and all sites screen hundreds of potential participants per year. Further, Site PIs [name] (Harvard Medical School) and [name] (University of Iowa), are internationally recognized experts in geriatric neuropsychology/psychiatry and have access to large, established cohorts of older participants. Sites will also make specific efforts to reach out to community dwelling individuals with age related cognitive decline who are not regular visitors to their clinics in order to improve the prospective validity of the participant sample. Additional recruitment methods include public presentations about the trial, brochures and flyers that describe the study and include information regarding inclusion/exclusion criteria as well as mechanism for indicating interest and communicating desire to be contacted. All materials used for advertising or recruitment will have received IRB approval prior to implementation, and the study sites will conform to recruiting standards established at each site.

### Repeated assessment battery

Once a participant is deemed eligible for participation based on their V0 results, they are next scheduled for their baseline session on the repeated assessment battery (V1), which takes approximately two hours. After completing this baseline assessment, participants are randomly assigned to either experimental or control training conditions (see below). Then, following the program set-up visit and after completing the first half of the training sessions, they will be administered an abbreviated mid-training assessment (V1.5) comprised of mindfulness-related measures. Immediately after total training is completed, participants are re-administered the baseline assessment battery (V2) and again after a three-month no contact period (V3).

### Primary and secondary outcome measures

#### Primary outcome

The primary outcome is a composite executive function measure composed of the neuropsychological assessments shown to capture executive functions that were not the focus of training (i.e., assessments that do not directly require sustained inhibitory control, the mode of training), including:Trails B (time to complete, raw score)DKEFS verbal fluency (total accurate switches, raw score)Auditory Consonant Trigrams (sum of accurate recalls following 9 s, 18 s and 32 s delays, raw scores)WAIS Digit Span (sum of accurate backward recalls, raw score)Attentional Blink task (second target accuracy, raw score)Category Switch task (reaction time: incongruent – congruent trials, raw scores)

The composite will be calculated by z-transforming each score and averaging across the six measures.

The primary composite executive function outcome is comprised of executive function measures. First, the Attentional Blink Task, in which participants must identify two target characters presented in rapid succession amongst related distractors. This task assesses participants’ attentional resource allocation distributed over time, as well as working memory encoding and distractor inhibition. We will also include Trails B, a common set-switching task in which participants must rapidly alternate between sequencing letters versus numbers. The Auditory Consonant Trigrams (ACT) test, a complex working memory task requiring participants to remember three letters over delay periods of 9, 18, or 36 s while counting backwards by threes from a given number. Also, the WAIS-IV Digit Span task backwards recall subtest, will be used to assess complex working memory span; participants are required to recall an increasing span of numbers in reverse order to that presented. Finally, participants will be required to complete a speeded Category Switch task, in which explicit rules (e.g., color, shape) direct the participant to accurately and rapidly identify and categorize serially presented objects.

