The primary executive function outcome measure is a composite measure composed of the main neuropsychological assessments, specifically includingTrails B (raw score) – Trails A (raw score)DKEFS verbal fluency (switching raw score)Auditory Consonant Trigrams (sum of 9 s, 18 s and 32 s delay raw scores)WAIS Digit Span (backward raw score)Attentional Blink task (second target accuracy, raw score)Category Switch task (incongruent – congruent trials reaction time)

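### The published rule for the primary composite averages two lower-is-better scores with four higher-is-better scores and states no sign reversal

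*Protocol article*

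**What the plan says.** The protocol article has a single primary outcome, a composite of executive function. The Primary outcome section names the six components and how each is scored:

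- "Trails B (time to complete, raw score"
- "DKEFS verbal fluency (total accurate switches, raw score"
- "Auditory Consonant Trigrams (sum of accurate recalls following 9 s, 18 s and 32 s delays, raw scores"
- "WAIS Digit Span (sum of accurate backward recalls, raw score"
- "Attentional Blink task (second target accuracy, raw score"
- "Category Switch task (reaction time: incongruent – congruent trials, raw scores"

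It then gives the combination rule: "The composite will be calculated by z-transforming each score and averaging across the six measures".

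The Data analysis section repeats the six components without the averaging rule. There the first component is Trails B minus Trails A, and the last is again a reaction-time difference: "Category Switch task (incongruent – congruent trials reaction time". The same section tests the outcome by the group-by-time interaction in a linear mixed model at p < 0.05, with V2 as the primary time point. It takes a significant result on the composite as support that the intervention improves executive function.

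Neither section says that any component is reversed or otherwise aligned in direction.

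**The concern.** The article fixes the inputs, the transformation and the way of combining them, so a reader can apply the rule exactly as written. Applied that way, it gives a score without a single direction. A shorter Trails time and a smaller Category Switch cost are better performance, yet each lowers the average. More accurate switches, more recalls, a longer backward span and higher second-target accuracy raise it.

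Two parts of the article need a composite on which higher means better. The sample-size reasoning under Strengths describes benefit as an upward move on an index score (5.8 points against 1.0). The interpretation rule in Data analysis reads significance as improvement. With mixed signs, neither the size nor the sign of the interaction carries that meaning.

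The two affected components are both switching tasks, and Strengths names set switching as an area where earlier studies of the training showed benefit. If treatment improved only those two tests, by g standard deviations each, the literal composite would move by -2g/6 = -g/3, which would look like harm.

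**Working it through.** **Inputs from the article.** Six components, equally weighted (Primary outcome). Design effect d = 0.50 on the between-group difference in change, and 120 participants (Strengths). Allocation 1:1, hence 60 per arm (Randomization; Overall design and timeline). Significance at p < 0.05 (Data analysis).

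**Assumptions not in the article.** The test is two-sided. All six components have the same standardised gain g and the same variance. After alignment, every pair has the same correlation r on the scale on which d is defined. Values of r = 0, 0.3 and 0.5 show the range.

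**The plan's own figure.** The article states no power, so the total of 120 cannot be strictly reproduced. At d = 0.50 and 60 per arm, two-sided 5%, power is 78.2% by the normal approximation and 77.5% by the noncentral t. A total of 126 would be needed for 80%. The article's worked example gives (5.8 - 1.0)/10 = 0.48, for which power is 74.8%. The sign point does not depend on these figures; they are only the baseline.

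**Direction of each component.**

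| Component | Better performance is | Sign in the average as written |
|---|---|---|
| Trails (B, or B minus A) | lower | - |
| Verbal fluency switches | higher | + |
| Auditory Consonant Trigrams | higher | + |
| Digit Span backward | higher | + |
| Attentional Blink accuracy | higher | + |
| Category Switch cost | lower | - |

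**Mean effect.** Aligned: 6g/6 = g. As written: (4g - 2g)/6 = g/3.

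**Variance.** Aligned: (6 + 30r)/36. As written, of the 15 pairs, 7 have like signs (6 among the four, 1 among the two) and 8 have opposite signs. The variance is therefore [6 + 2r(7 - 8)]/36 = (6 - 2r)/36.

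**Ratio of standardised effects, as written to aligned:** (1/3) × sqrt[(6 + 30r)/(6 - 2r)].

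- r = 0: (1/3) × sqrt(6/6) = 0.333
- r = 0.3: (1/3) × sqrt(15/5.4) = 0.556
- r = 0.5: (1/3) × sqrt(21/5) = 0.683

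**Consequence for d = 0.50 with 60 per arm** (two-sided 5%, normal approximation):

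| r | d as written | Power as written | Total N for 80% power |
|---|---|---|---|
| 0 | 0.167 | 14.8% | 1132 |
| 0.3 | 0.278 | 33.1% | 408 |
| 0.5 | 0.342 | 46.4% | 270 |

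**Simulation check.** With 4,000 simulated trials per value of r, power was 79.0%, 77.0% and 76.8% for the aligned composite. It was 15.0%, 32.3% and 45.5% for the composite as written.

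**The case against.** The best defence is that this is silence in a condensed article. It does not say that the components keep their raw sign; the word raw describes the test scores before transformation. Aligning direction is a scoring step that the full protocol or analysis plan may well contain. The article's purpose also points that way, since calling the result a measure of executive function and reading significance as improvement make sense only for an aligned score.

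Much of this stands. A reader might infer that the trial will analyse a mis-signed endpoint, and the article does not show that. The defence does not remove the point, however. The article gives a complete recipe for its only primary outcome, and the recipe followed exactly produces the wrong score. That goes beyond leaving out a detail.

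Three further inferences are tempting and should not be drawn:

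- **That the timed tests cancel the other four.** Under equal gains the offset is partial. Full cancellation needs 4a = 2b, so average gains on the two timed tests (b) would have to be twice those on the others (a).
- **That most of the power is lost in every case.** At r = 0.5 about 59% of it remains (46.4/78.2).
- **That the rule is also defective because it names no reference mean and SD for the z-scores.** An article commonly leaves that choice to the analysis plan, and it is not part of this point.

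**Conclusion.** The point holds for the published rule: two of six components run opposite to the rest, and no reversal is stated. Under literal execution and equal gains, the composite keeps one third of the mean gain. The standardised effect falls to between one third and about two thirds of its aligned value for r from 0 to 0.5. Power falls from about 77% to between about 15% and 46%.

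These figures rest on literal execution, equal gains and variances, a common correlation and a two-sided test, none of which the article gives. The article also applies d = 0.50 to an outcome measure in general, not to this composite by name. The size of the loss is therefore illustrative; the direction problem does not depend on it. Because it concerns the sole primary endpoint and is easily repaired, the wording should be settled before any unblinded analysis.

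**What to change.** Add one sentence to the Primary outcome section, directly after the averaging rule: the z-scores of the Trails component and of the Category Switch reaction-time cost are multiplied by -1 before averaging, so that a higher composite means better executive function on all six measures.

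The Primary outcome and Data analysis sections define the Trails component differently (B alone, and B minus A). That needs reconciling in its own right, but both versions improve downwards, so the reversal applies whichever is kept. The Data analysis list has no averaging rule and needs no sign statement beyond a reference back.

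The cost is one sentence, with no new data and no change to sample size or visits. If the full plan already contains the reversal, only the published description needs correcting.

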#### Secondary outcomes

The first set of secondary outcomes comprises measures of cognition, learning and memory; primarily standardized neuropsychological assessments, including:Gradual onset Continuous Performance Task (target accuracy, raw score)Stop Signal task (time interval for successful stop, raw score)Flanker task (reaction time: incongruent flanker trials – congruent flanker trials, raw scores)Cross-modal Stroop – Mixed Signals (reaction time: response conflict trials, raw score)WAIS IV Digit Span, forwards and sequencing (raw scores)Spatial Working Memory task (accuracy, raw score)DKEFS Verbal Fluency, phonemic and semantic subtest (raw scores)Reinforcement Learning task (bias index)WMS IV Logical Memory I & II immediate recall (sum of learning trials, raw score)WMS IV Logical Memory I & II delayed recall (sum of recall trials, raw score)

Even though some of these measures may engage executive functions (e.g., gradual onset continuous performance task may engage inhibitory control), we chose not to include measures that were very similar to the training in the primary outcome. This is an effort to avoid the criticism that the primary outcome measure is overly influenced by improvements in near transfer tasks.

The second set of secondary outcomes comprise measures of functional performance, quality of sleep, quality of life and mindfulness; and include self-report and directly-observed functional performance measures:Walking Behavior Measure (raw score)Self-efficacy Assessment (two scales, raw scores)Falls Efficacy scale (raw score)Timed Up and Go task –TUG (time to completion, raw score)SF-12 (raw score)Cognitive Failures Questionnaire (raw score)Pittsburg Sleep Quality Index (raw score)Mindful Attention Awareness Scale – MAAS (raw score)Breath Counting task (accuracy, raw score)

**The secondary outcome –** cognition is comprised of measures of cognition including response control, captured by the Gradual Continuous Performance Task (GradCPT) [36, 37]; participants must sustain engagement (i.e., no inter-trial break), frequently respond to foil images and exert inhibitory control to overcome the proponent motor response when presented with an infrequent target image (i.e., withhold response). Also, the stop signal task, in which participants must inhibit a triggered response (i.e., go signal) when a *stop signal* (e.g., tone or color) is presented after the onset of the trigger. The Flanker task [38], in which participants must quickly identify the direction of a central arrow flanked by either congruent (i.e., facing the same direction as the central arrow) or incongruent arrows; and necessarily inhibit the influence of incongruent flanking stimuli. A cross-modal Stroop task, Mixed Signals (BrainHQ.com), requires participants to rapidly overcome interference from competing responses and information from conflicting stimulus modalities. WAIS-IV Digit Span (forward and sequencing subtests) is a verbal working memory span task, where the subject is given a list of numbers to remember and instructed to repeat the numbers either in the same order (digits forward subtest) or canonical order (sequencing subtest). In the Spatial Working Memory task participants are presented with several possible target locations displayed centrally along the vertical meridian. Following each trail, the participant is presented with a probe to a single location to which they must decide if the given location was included in the possible target locations (yes/no) [39]. The DKEFS Verbal Fluency, semantic and phonemic cueing subtests will also be included to examine broad executive function ability requiring spontaneous and rapid generative fluency. Scoring is based on the number of accurate replies per cue type (phonemic, semantic) and response characteristics (e.g., intrusions, perseverative errors) are also scored.

**The secondary outcome -** learning and memory is comprised of two tasks that examine learning rate via the Reinforcement Learning Task, designed and developed by [name] [40], as well as acquisition and short and long delay free, cued and recognition memory performance via Logical Memory I & II (WMS-IV).

**The secondary outcome** - functional performance is comprised of performance on a directly observed measure as well as self-report questionnaires. For self-report, we will use the Walking Behavior measure, in which participants are asked to report the numbers of times (and duration of time) that they spent brisk walking per week. The Self-efficacy assessment, which is comprised of two measures, way-finding self-efficacy and self-efficacy for walking [41], will provide insight into participants’ perceived sense of direction [42] and self-efficacy for navigation [43]. The Falls Efficacy Scale [44] provides a valid and reliable measure of *confidence* when engaging in various daily activities (e.g., get out of bed, take shower). Finally, we will employ a directly observed measure, the Timed Up and Go (TUG) task [45], which assesses general mobility and balance.

**The secondary outcome -** quality of life is comprised of performance on the Short-Form 12 (SF-12v2) [46], a measure of Health-Related Quality of Life. This assessment serves as a measure of the impact of program use on the participants’ own view of their impairment and function (i.e., quality of life). The Cognitive Failures questionnaire will also be administered to evaluate common errors in daily activities that may affect quality of life.

**The secondary outcome -** quality of sleep is comprised of performance on the Pittsburg Sleep Quality Index. This measure has been used in many outcomes studies including a prior study of TAPAT outcomes in veterans with PTSD in which it effectively captured improvements in sleep quality post-training compared to a waitlist control group [47].

**The secondary outcome –** mindfulness includes two measures that will be included in the mid-training assessment to assess mindfulness and awareness. The Mindful Attention Awareness Scale (MAAS) is a valid measure for mindfulness. The second is a breath-counting task [48], serving as a behavioral measure of mindfulness.

